## Abstract

**Background:**

Cold hands sensation is a common disorder within the Korean population. Many Korean family physicians believe that it is a mild early manifestation of Raynaud’s phenomenon (RP), or may be related to RP. RP is characterized by reversible digital vasospasm provoked by cold temperatures and/or emotional stress, and doctors often prescribe medications that are used in treatment of RP for subjects with cold hands. However, this has not shown a clear benefit, and these medications can cause unwanted side effects. It is also reported that traditional Korean medicine, including acupuncture, is widely used to treat cold hands, although the current level of evidence for this approach is also poor and to date, there have been no published randomized controlled clinical trials (RCTs) evaluating the efficacy and safety of acupuncture for cold hands. We have therefore designed a pilot RCT to obtain information for the design of a further full-scale trial.

**Methods/Design:**

The proposed study is a five-week pilot RCT. A total of 14 subjects will be recruited and randomly allocated to two groups: an acupuncture plus medication group (experimental group) and a medication-only group (control group). All subjects will take nifedipine (5 mg once daily) and beraprost (20 mg three times daily) for three weeks. The experimental group will receive additional treatment with three acupuncture sessions per week for three weeks (nine sessions total). The primary outcome will be measured using a visual analogue scale. Secondary outcomes will be measured by blood perfusion in laser Doppler perfusion imaging of the hands, frequency and duration of episodes of cold hands, and heart rate variability. Assessments will be made at baseline and at one, three, and five weeks thereafter.

**Discussion:**

This study will provide an indication of the feasibility and a clinical foundation for a future large-scale trial.

**Trial registration:**

This study was registered at Korean Clinical Research Information Service (CRIS) registry on 5 August 2013 with the registration number #KCT0000817.

## Background

One of the normal physiological responses to cold temperatures or emotional stress is a reduction of the skin temperature to preserve body heat and maintain a normal body core temperature. Reactions characterized by excessive peripheral vasospasm may evoke clinical symptoms, and complaints of cold hands sensation are very common among the general population [1]. Cold hands sensation is defined as hands that become intolerably cold when exposed to normal temperature, in which most individuals feel no cold. There can be a confusion between cold hands sensation and Raynaud’s phenomenon (RP), as both have cold hands as a symptom. The signs of RP include cold and numb hands when exposed to cold temperatures, with subsequent pain and skin becoming blue in colour [2]. In a community-based survey of approximately 7,000 people, almost 12% responded that they had experienced unusual sensitivity to cold temperatures in their fingertips or toes [3, 4]. This may be due to a mild, early manifestation of Raynaud’s phenomenon (RP) or may be related to RP [1, 5], which is characterized by a reversible digital vasospasm provoked by cold temperatures and/or emotional stress [6]. A study by Choi *et al*. [7] found that in South Korea, 43% of patients with an abnormal cold sensation in the hands or feet had RP, and that primary RP represented 73% of cases of RP, and many family physicians prescribe medications for cold hands sensation based upon treatment recommendations for RP [8].

The exact prevalence of primary RP is unknown. It is a common disorder, especially in the general practice setting [9], and its prevalence is thought to be high compared with the low number of patients who seek treatment for it [10]. The treatment is mostly dependent on the etiology of the disorder and on the presence and severity of the individual symptoms. Lifestyle modifications including avoidance of cold exposure and caffeine, discontinuation of smoking, and sufficient body insulation, are the first line of treatment for the prevention of vasospasm [11, 12]. If these modifications are insufficient, calcium channel blockers are the most widely used pharmacological agents for treatment [4, 13, 14], and in severe forms of RP, prostaglandins, endothelin-1 receptor antagonists, and specific inhibitors of phosphodiesterase-5 are the treatments of choice [6]. Although a wide variety of medications are used for treatment of RP, none have been shown to have a clear benefit, and all may be associated with unwanted side effects including headache, flushing, and dizziness. There is currently no gold standard or universal guideline for the treatment of RP [6, 15].

In Korea, traditional treatments including acupuncture and herbal medications have been widely used to treat cold hands for many years, and there are a number of published reports regarding these treatments for cold hands [16–18]. Nonetheless, the present level of evidence is poor because of small sample sizes or short durations of these published studies. In addition, even though there are a few published randomized controlled trials (RCT) regarding acupuncture and RP [19, 20], there is no published RCT evaluating the efficacy and safety of acupuncture in subjects with cold hands sensation. The need remains for more rigorous studies that will elucidate the efficacy and safety of acupuncture for subjects with cold hands sensation. The aim of the present study was to collect preliminary data on acupuncture compared with conventional pharmaceutical agents alone for the treatment of cold hands sensation. The results of this study will provide evidence for the feasibility of this trial design as well as basic data for a large-scale RCT of acupuncture for subjects with cold hands sensation.

### Hypotheses

In this randomized controlled two-arm clinical trial, we will evaluate the acupuncture treatment as an adjunct therapy to cold hands sensation. The hypothesis is that the addition of acupuncture treatment to medication reduces the severity of cold hands sensation (measured using a visual analogue scale (VAS)) significantly more than medications alone.

## Methods/Design

### Design

The study is a randomized controlled pilot clinical trial. It is designed to obtain basic information of a further full-scale trial about acupuncture treatment in subjects with cold hands sensation. The protocols to be used adhere to the principles of the Declaration of Helsinki and have been approved by the Institutional Review Board of Daegu Catholic University Hospital (approval number IORG0004453), where the study will take place. The trial is registered with the Korean Clinical Research Information Service (CRIS) registry. Written informed consent will be obtained from each participant before any treatment is given.

The outcome assessments and statistical analyses will be performed by professionals blinded to the assignment of subjects. The trial process is presented in Figure 1. The trial will run for five weeks. Subjects will be randomly allocated to one of two groups, a control group, in which subjects will receive only medication for three weeks, and an experimental group, in which subjects will receive the same medication as well as nine acupuncture sessions (three sessions per week for three weeks). Assessments will be made at baseline and again at one, three, and five weeks thereafter. The five-week assessment will be performed two weeks after treatment cessation. This study will be conducted between late November 2013 to February 2014 which is winter season in South Korea. We will record room temperature to control for temperature bias in this clinical trial.

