### Participants

A target sample size of 14 subjects with cold hands sensation has been set. One of the main objectives of this study is to provide an estimate of the sample size required for the full-scale randomized controlled clinical trial.

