### Statistical analysis

The statistical significance level will be set at 5%, and the data will be processed with the last observation carried forward method for the intention-to-treat analysis. Statistical analysis in this study will be performed using IBM SPSS Windows version 19.0 statistical software (IBM Co., Armonk, NY, USA) and will be based on the Korean Clinical Trial Statistics Guidelines.

The study will identify the comparative equivalence of demographic variables and clinical characteristics between the experimental and control groups by performing the two sample t-test or Mann-Whitney U test if normality test is satisfied or not for continuous data, chi-square test for categorical data.

A repeated measure two-factor analysis will be performed to identify differences in VAS, blood perfusion, frequency and duration of cold hands sensation attacks and HRV scores between the experimental and control group based on time (baseline, weeks one, three, and five). If the interaction between group and time is statistically significant, the point at which the pattern of results between the two groups changes will be checked using the contrast analysis. To compare groups and the incidence frequency of adverse events related to acupuncture and medication, the chi-square test will be used.

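### Room temperature is recorded to control temperature bias, but the stated group-by-time analysis never uses the readings and no room condition is described

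*Protocol article*

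**What the plan says.** Design (protocol article) places the trial in one cold season: "This study will be conducted between late November 2013 to February 2014 which is winter season in South Korea". The next sentence gives the temperature measure and its purpose: "We will record room temperature to control for temperature bias in this clinical trial". It does not say which room is meant, at which visits the reading is taken, whether a range must be kept, or what is done with the values.

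Statistical analysis gives one approach for all efficacy outcomes: "A repeated measure two-factor analysis will be performed to identify differences in VAS, blood perfusion, frequency and duration of cold hands sensation attacks", and HRV, with the comparison made "between the experimental and control group based on time (baseline, weeks one, three, and five"). Contrasts follow "If the interaction between group and time is statistically significant". No covariate is named.

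On size, Participants says: "A target sample size of 14 subjects with cold hands sensation has been set". Randomization describes block randomization without giving the ratio or block size.

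**The concern.** Recording a variable does not control for it. Control comes either from the conditions of measurement, by holding the room within limits, or from the analysis, by adjusting for the reading. The article states a purpose that needs one of these and describes neither.

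Temperature is not a side issue in this trial. The Background explains the condition as an excessive vascular reaction to cold, and skin perfusion of the hands is an outcome. In a sample of 14, the arms can differ by chance in the temperature at which they were scanned, and visit-to-visit variation in the room adds noise to perfusion and possibly to HRV. A later report could say that temperature was controlled when the prespecified analysis never used the readings.

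**Working it through.** **Text check.** The article gives no figure on this point to reproduce, so the first step is to look for temperature wherever it could enter as a measurement, covariate, stratification factor or test condition.

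- Design: room temperature is recorded, with control as the purpose.
- Randomization: no temperature-related or calendar-related factor is named, only blocks.
- Table 1 (schedule): VAS, blood perfusion, episodes and HRV are listed; room temperature is not.
- Blood perfusion: scan size, resolution and timing are given; no room temperature or acclimatisation period.
- Heart rate variation: an eight-hour restriction on drugs, caffeine, tobacco and alcohol is given; no room condition.
- Statistical analysis: group, time and contrasts; no temperature term.

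Design and Statistical analysis therefore do not meet: the purpose is stated in one, and nothing in the other serves it.

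**Which outcomes the readings can reach.** Perfusion and HRV are measured with equipment at a visit. If the recorded room is the assessment room (an assumption, since the article does not say), its temperature is the exposure at that measurement. The VAS is rated for each episode, and frequency and duration come from patient diaries. A reading in the assessment room is not the exposure behind those episodes.

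**Chance imbalance.** Inputs: 14 subjects (Participants); 7 per arm (assumption, ratio not stated); independent readings with standard deviation SD_T (assumption, no value in the article).

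- Difference in mean temperature between arms at one visit: SD = SD_T × sqrt(1/7 + 1/7) = SD_T × sqrt(2/7) = 0.53 SD_T.
- With SD_T of 0.5, 1 or 2 °C (assumed range): 0.27, 0.53 or 1.07 °C.
- Difference in change from baseline, if readings are also independent across visits: SD = SD_T × sqrt(4/7) = 0.76 SD_T, that is 0.38, 0.76 or 1.51 °C.

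**What adjustment could gain.** As a guide, take a single visit with 14 subjects in two arms: 12 residual degrees of freedom without the covariate, 11 with it. If temperature explains a share R² of the within-arm variance, the ratio of adjusted to unadjusted standard error is about sqrt((1 − R²) × 12/11).

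| R² (assumed) | Ratio |
|---|---|
| 0.1 | 0.99 |
| 0.2 | 0.93 |
| 0.3 | 0.87 |
| 0.4 | 0.81 |

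The ratio equals 1 when 1 − R² = 11/12, so R² = 1/12, about 8%. Below that, the covariate costs more than it returns. The formula omits the extra variance that arises when the arms differ in mean temperature, so it is slightly favourable to adjustment. It describes one visit, not the repeated-measures model proposed below, and should be read only as an order of size.

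**The case against.** The strongest reply is that control need not mean a covariate. It may mean checking or holding the test-room conditions, and the single winter season already limits variation. The article is condensed; a room procedure or a sensitivity analysis may stand in the full protocol or the analysis plan, which are not shown. This stands as far as it goes. A reader might infer that temperature control is absent from the trial altogether, and the documents do not support that. They support only that no control is described and that the stated analysis contains none. The article does make the positive claim, however, and the action it attaches to the claim is recording.

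A second reply is that an unadjusted randomized comparison is valid. This also stands. A reader might infer that the treatment effect is biased, but block randomization gives no reason to expect room temperature to differ systematically between arms, and chance imbalance is already part of the standard error. What remains is precision.

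A third reply is that the analysis is not called an ANOVA, so its inability to take a covariate that changes at each visit is an inference. That is correct. The classical form is the likely reading of a two-factor repeated-measures analysis, and that form does not accommodate such a covariate.

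Finally, this is a small pilot, and neither the significance level nor the sample size is affected. That limits the weight of the point but does not remove the mismatch.

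**Conclusion.** The point holds in a limited form: the stated control and the stated analysis do not match. The cost is chance imbalance and lost precision with 14 subjects, mainly for laser Doppler perfusion and HRV. It is not systematic bias, and the primary VAS comparison is not helped by these readings either way.

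The size depends on assumptions: 7 per arm, independent readings, and readings taken in the assessment room. On these, the between-arm temperature difference at a visit has a standard deviation of 0.53 times that of the readings. The gain from adjustment runs from about nothing at R² = 0.1 to a standard error about 19% smaller at R² = 0.4.

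Two further steps are tempting and should not be taken. One is to turn the temperature imbalance into a percentage error in perfusion: the article gives neither the spread of room temperature nor the response of perfusion to it. The other is to require adjustment of VAS and diary outcomes for outdoor weather: the article does not plan to collect such data, and its claim concerns room temperature only.

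**What to change.** For perfusion and HRV, add a mixed model with group, visit, their interaction and the baseline value, and include the room temperature at each visit as a time-varying covariate. State whether this is the main or a supportive analysis for those outcomes, and fix it before results are seen by group. Treatment cannot affect the room temperature, so adjusting for this post-randomization reading is safe. Fit the model to observed visits, so that a value carried forward is not paired with a temperature at which it was not measured.

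In Design, limit the claim of temperature control to perfusion and HRV. If the adjusted analysis is not wanted, describe the readings as monitoring only. If room conditions were in fact held within limits, say so and give the limits.

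The cost is one degree of freedom per model and a different model class for these secondary outcomes. No new data are needed if a reading is logged with each assessment. Recruitment is reported as finished (Trial status), but both the analysis and the wording can still be settled if results by group have not yet been seen; otherwise the adjusted analysis should be labelled post hoc.

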**Figure 1 Fig1:**
[figure not shown]
**Flow chart of the pilot randomized controlled trial.**

### Recruitment

Participants will be recruited through advertisements on hospital websites and on bulletin boards. If subjects are interested in participating, they will be invited to the hospital for a screening meeting. Eligibility will be determined by a vascular surgeon based on the results of physical and photoplethysmography examinations. If eligible, subjects will be guided through the informed consent process. After written consent is obtained, a study researcher will randomly allocate each participant to one of the two treatment groups.

### Participants

A target sample size of 14 subjects with cold hands sensation has been set. One of the main objectives of this study is to provide an estimate of the sample size required for the full-scale randomized controlled clinical trial.

### Inclusion criteria

Participants must meet the following criteria for inclusion in the study: cold hands sensation or RP, photoplethysmography showing decreased arterial pulse amplitude or abnormal ischemic pulse waveform such as biphasic or monophasic wave, aged between 20 and 75 years, VAS score of >3 for cold hands sensation, symptom duration of least one month, available for follow-up during the entire trial period, and provide written informed consent.

### Exclusion criteria

Participants will be excluded from the study if they meet any of the following criteria: one or more ulcerated fingers, acute ischemic disease requiring reperfusion surgery, high bleeding tendency due to anticoagulant medications, significant renal or hepatic disease, severe psychiatric or psychological disorders, known hypersensitivity reaction to acupuncture treatment, alcohol and/or drug abuse, pregnant, lactating, or planning pregnancy, any individual deemed ineligible by a physician, refusal to participate in the trial or to provide informed consent, or an inability to comprehend or express oneself in the Korean language.

### Randomization

Subjects will be randomized using a computerized random number generator by an independent statistician who is blinded to subject assignment. The method which we use for randomization concealment is sequentially numbered, opaque sealed envelopes. Block randomization will be performed once a participant’s eligibility is confirmed and written informed consent has been obtained. Treatments will be scheduled after randomization.

### Interventions

Subjects will be randomly divided into two treatment groups: an experimental group (acupuncture plus medication group) and a control group (medication only group). The medication will be administered every day for three weeks and the acupuncture sessions performed three times per a week for three weeks (nine times in total). There are no other interventions such as moxibustion, exercises, or lifestyle advice in this study.

#### Medications

Oral nifedipine (calcium channel blocker, 5 mg once daily) and beraprost (prostaglandin analog, 20 mg three times daily) will be prescribed for all subjects in both groups.

#### Acupuncture treatment

The following acupoints will be used based on previously published work [21]: unilateral GV20, bilateral ST36, PC6, TE5, LI4, and EX-UE9 (extra points). In total, 17 acupoints will be used. Sterilized disposable acupuncture needles (DongBang Acupuncture Inc., Korea) 0.25 × 40 mm in size will be manually inserted into each of the acupoints. After needle insertion, the *deqi* sensation will be induced by manual stimulation. The needles will be inserted for 20 ± 5 minutes and then removed. Acupuncture will be practiced by Korea Medical Doctors (KMD) who are licensed by Ministry of Health and Welfare.

### Data collection

In this study, the primary outcome will be measured by VAS. The secondary outcomes are changes in microvascular blood perfusion, frequency and duration of cold hands sensation episodes, and heart rate variability (HRV) measurements. Both primary and secondary outcomes will be assessed at baseline and at one, three, and five weeks after initiation of treatment. The treatment and outcomes measurement schedules are presented in Table 1.

**Table 1 Tab1:** **Schedule of treatments and outcome measurements throughout the five-week randomized controlled trial**

		Baseline	Treatment period									Follow-up period	
		Week 0	Week 1			Week 2			Week 3			Week 4	Week 5
Measurement	VAS	√	√						√				√
	Blood perfusion	√	√						√				√
	Frequency and duration of cold hands episodes	√	√						√				√
	HRV	√	√						√				√
Treatment	Medication		√			√			√				
	Acupuncture		√	√	√	√	√	√	√	√	√		

HRV: Heart rate variability, VAS: visual analogue scale.

#### Primary outcome measurements

##### VAS

The severity of cold hands sensation episodes ranges across a continuum of values but cannot easily be measured directly. Therefore, we will use a 10-cm VAS as the measurement instrument to determine the severity of cold hands sensation. Each subject will rate each episode of cold hands sensation on a scale of 0 to 10, where 0 indicates the absence of the cold hands sensation and 10 indicates the worst cold hands sensation imaginable. VAS measurements will be made at baseline and at one, three, and five weeks thereafter.

#### Secondary outcome measurements

##### Blood perfusion

Laser Doppler perfusion imaging (LDPI) with a Perimed AB LDPI system (Perimed AB, Jaerfaella, Sweden) will be used to measure the perfusion of microcirculation in the skin of the hands. The LDPI system has a moving laser beam that scans the tissue in steps and a photo detector that measures the backscattered light. The frequency shift of the light has a direct relation to the perfusion of the lighted area of skin, according to the Doppler principle [22].

The largest scanning image is 64 **×** 64 (4096) points and low, medium, and high resolution modes are available. The largest scanning area is about 20 **×** 20 cm. Measuring time is about 50 milliseconds per point, and 4 minutes for a 64 **×** 64 image. A normal photo is taken along with the blood perfusion scan in order to localize the area of interest. When the scan is completed, the region of interest is selected for analysis of the mean blood perfusion and its changes using the built-in LDPI windows 2.5 software.

